#### **B. Mosquito collections**

BioGents Gravid Aedes Traps that capture adult *Aedes aegypti* via a sticky insert, will be deployed in each of the schools and monitored weekly for one year.

In addition, based on the four area types, 100 houses will be randomly selected to collect samples of *Aedes aegypti* mosquitos at home during the rainy summer period May to September. 100 children will be provided with a mosquito-trapping device. For trapping mosquitoes, we will use Gravid Aedes Traps (GATs) with a sticky insert to catch and count mosquitoes. GATs are essentially a black plastic bucket (with a hole two-thirds way up to let excess rainwater flow out) in which we place water with hay/dried grass. A double netting prevents the mosquitoes from actually laying their eggs in the hay infusion and a sticky insert glues the mosquitoes. These traps will be placed in areas protected from rain and direct sunlight. Depending on whether the school is open to the outside or not, GATs will be placed indoors and outdoors. Likewise for the homes, GATs will be placed such that they will not get knocked over/stolen. GATs will be monitored daily by school teachers/students to ensure they do not dry out, are attacked by ants/geckos etc and the sticky strip will be replaced once a week and placed into a ziplock type plastic bag with information on date and address written in indelible ink on the bag. The bags will then be stored in a reasonably cool room and then collected by the entomologists within a reasonable delay.

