| 14. Study timeline                      | 
Estimated start date of enrollment: 01/06/2024
 
Enrollment period: 6 months
 
Duration of subject's participation:
 
 
- 4 months for mosquito sampling study
 
- 1 day for seroprevalence study and questionnaire
 
 
Total estimated study duration: 1 year
 
Data analysis: 6 months
 
Data storage period: 2 years after the last publication
 |
| 15. Number of centres                   | 8-12 schools                                                                                                                                                                                                                                                                                                                                                                                                                          |
| 16. Expected results                    | Sero-prevalence rates for dengue and chikungunya stratified by age, sex and environmental typology (4 types: High vs. Low centrality and High vs Low vegetation) of home and school. Mosquito abundance according to environmental typology. KAP on dengue and chikungunya.                                                                                                                                                           |

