### **6.2. Sample flow**

#### **A. Labelling**

The mosquito sticky paper catches will be changed weekly and placed into a ziplock bag with the date and address written in indelible ink on the outside of the bag and collected as soon as possible (days) by the entomological team.

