#### **B. Shipment**

The mosquito sticky catches will be transferred to the entomology laboratory at Chulalongkorn University and identified to species and gender. Once identified and entered into the computer the samples will be disposed of. Once the mosquito sampling is complete, as above, the school/house address will be transformed into one of the four environmental categories. The address will then be erased.

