## 9. STATISTICAL CONSIDERATIONS

Sample size:

Based on the preliminary data showing a difference in prevalence rates according to school centrality and environmental typology (approximately 26% vs 15%), we estimate a necessary sample size of ~210 children for each of the four typologies (Central+/Environmental+, Central+/Environmental-, Central-/Environmental+, Central-/Environmental-).

Sample size was calculated as follows [17]

$$n = (Z_{\alpha/2} + Z_{\beta})^2 \cdot [p_0(1 - p_0) + p_1(1 - p_1)] (p_0 - p_1)^2$$

Where n is the required sample size per treatment arm,  $Z_{\alpha}$  and  $Z_{\beta}$  are constants set by convention according to the accepted  $\alpha$  error and whether a one-sided or two-sided effect,  $p_0$  is the proportion sero-positive in area type 0 (ie Central + or Environment +), and  $p_1$  the proportion areas type 2 (Central – or Environment –).

Assuming a  $p < 0.05$  as acceptable and a study with 90% power, the following constant values are:  $Z_{\alpha/2} = 1.96$  and  $Z_{\beta} = 0.84$ .

Because our preliminary data indicated variation within school centrality and environmental typology, (coefficient of variation ranging from 0.6-1), we used the following formula to estimate the number of different sites for each typology.

$$\text{Site number per typology} = 1 + (Z_{\alpha/2} + Z_{\beta})^2 \cdot [p_0(1 - p_0)/n + p_1(1 - p_1)/n + k^2(p_0^2 + p_1^2)] (p_0 - p_1)^2$$

Where k is the coefficient of variation and n the number of individuals as calculated above. Using  $n=210$  and  $k=0.6$  to 1, we would need at least two and optimally three schools per environmental typology with 80-100 children per school.

Sero-positivity (as defined by the manufacturers instructions) will be analysed by logistic regression with age, sex and centrality (high vs. low) and environmental typology (Open vs Dense) as explanatory variables using R. School mosquito densities will also be included as an explanatory variable. In the subset of individuals collecting mosquitoes in the homes will be taken into account in a separate analysis. Mosquito densities will also be analysed with respect to the environmental typology and meteorological parameters.

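### Trap position (indoor or outdoor) varies with the school building and is not among the recorded data described, so catches compared by typology may be confounded by placement

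*Protocol*

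**What the plan says.** **Placement in schools (Protocol, section 5.1 B).** "Depending on whether the school is open to the outside or not, GATs will be placed indoors and outdoors". A general condition applies to all traps: "These traps will be placed in areas protected from rain and direct sunlight".

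**Placement in homes (same section).** "Likewise for the homes, GATs will be placed such that they will not get knocked over/stolen". Nothing says whether a home trap stands inside or outside.

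**Label.** Section 5.1 B has the weekly sticky strip "placed into a ziplock type plastic bag with information on date and address written in indelible ink on the bag". Section 6.2 A repeats this: "placed into a ziplock bag with the date and address written in indelible ink on the outside of the bag". Neither lists a trap number or a position.

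**What happens afterwards (section 6.2 B).** Catches are discarded once identified and entered. Then "the school/house address will be transformed into one of the four environmental categories. The address will then be erased".

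**Use of the counts.** Section 9 states: "Mosquito densities will also be analysed with respect to the environmental typology and meteorological parameters". The same section puts school mosquito density into the logistic regression for seropositivity, beside centrality and the Open/Dense typology. The Summary of Protocol lists among the expected results "Mosquito abundance according to environmental typology", and section 5 names abundance by area type as the second aim.

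**The concern.** A comparison of catches between area types needs traps operated in the same way in each type, or a record of how they differed. The protocol provides neither for indoor versus outdoor position. In schools, position depends on the building. In homes it is left open apart from shelter and security.

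The building feature that drives placement may be related to the factor under comparison. The typology rests partly on the height and surface of buildings (section 1, pilot study), so densely built-up areas could hold more enclosed schools. If so, a difference in where traps stand would show up as a difference in mosquito abundance.

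Three uses are exposed: the abundance-by-typology result, the density covariate in the seropositivity model, and the empirically validated abundance on which the primary objective relies (section 2). Trap layout and label content are field procedures that the protocol itself fixes, and no later analysis plan can adjust for a position that nobody wrote down.

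**Working it through.** The protocol states no trap-count figure to reproduce. The check is a reading of the text, followed by an illustration on assumed values.

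**1. Does the layout differ between schools?** The rule is conditional on whether a school is open to the outside. Whether the sentence means one position or both at a given school is unclear, but on either reading the indoor/outdoor mix can differ between schools.

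**2. Is position recorded?** Both label descriptions (5.1 B and 6.2 A) list date and address only. If a school has traps in both positions, its bags for the same week carry the same label. Temperature and humidity loggers are fixed to the traps (section 7.1) and may partly reflect position, but they are at best a proxy. No section lists position as a recorded item.

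**3. Is placement tied to typology?** The Open/Dense class comes from satellite vegetation index and building height and surface (sections 1 and 7.1). Openness of a school building is a different attribute. A link is plausible but not stated.

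**4. Could chance alone unbalance it?** With 2-3 schools in each of four types, each Open/Dense level has 2 × 2 = 4 to 2 × 3 = 6 schools. Assume half of all schools have open buildings, unrelated to typology.
- 8 schools: exact balance (2 and 2) has probability C(4,2)²/C(8,4) = 36/70 = 0.51, so a 3-to-1 split or worse has probability 0.49.
- 12 schools: exact balance (3 and 3) has probability C(6,3)²/C(12,6) = 400/924 = 0.43, so a 4-to-2 split or worse has probability 0.57.
- A complete split is rare: 2/70 = 0.029 and 2/924 = 0.002.

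Some imbalance is therefore about as likely as not, even with no underlying link.

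**5. What could imbalance do?** Let r be the outdoor/indoor catch ratio per trap, and a and b the shares of traps outdoors in Open and Dense schools. With equal true density,

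apparent Open/Dense ratio = (a·r + 1 − a) / (b·r + 1 − b).

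All of r, a and b are assumptions.

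| a, b | r = 1.5 | r = 2 | r = 3 |
|---|---|---|---|
| 1, 0 | 1.50 | 2.00 | 3.00 |
| 1, 0.5 | 1.20 | 1.33 | 1.50 |
| 0.67, 0.33 | 1.15 | 1.26 | 1.41 |
| 0.5, 0.5 | 1.00 | 1.00 | 1.00 |

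Example: a = 0.67, b = 0.33, r = 2 gives (1.34 + 0.33)/(0.66 + 0.67) = 1.67/1.33 = 1.26. If indoor traps catch more, r falls below 1 and the direction reverses. The distortion disappears when the shares are equal, which is what a common layout secures.

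**The case against.** The strongest reply is that the protocol shows a loose field procedure and not a bias. Four parts of it deserve an answer.

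- **The wording is not an either/or rule.** A reader might infer that open schools get outdoor traps and enclosed schools get indoor ones. The sentence joins the two positions with *and*, so it may mean both wherever the building allows. This stands: the allocation is ambiguous. What remains is that the layout depends on the building.
- **Building openness is not the typology.** Because the word *open* serves for both, a reader might infer that placement follows the exposure by design. The typology is a landscape class, and no section ties it to school architecture. This stands: confounding is a risk, not a fact.
- **A trap log is not excluded.** A reader might infer that indoor and outdoor catches can never be separated. The label descriptions do not claim to be a full list of entomological records, and linking logger readings to catches trap by trap would need some trap identifier. This also stands, but no such record is described.
- **Homes are less exposed.** Each child receives one device, so catches from different traps should not be mixed under one address, and no stated rule makes home position vary with typology. This stands, although home position is still neither fixed nor recorded.

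It is also fair that mosquito numbers are a secondary criterion. The same counts, however, enter the seropositivity model.

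**Conclusion.** The point holds as a risk that is cheap to remove. School trap layout varies with the building, home position is not fixed, and position is not among the recorded data described. Comparisons of catches by typology, and the school-density covariate, may therefore be confounded by placement. This requires that building openness is related to the Open/Dense class or is unbalanced by chance among 4-6 schools per level, and that indoor and outdoor traps catch at different rates.

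The size and direction are unknown. The fold-differences above illustrate a mechanism. They are not estimates for this study, and taking them as such would treat building openness as if it were the typology. The seroprevalence estimates themselves are unaffected. The change should be made before trapping starts, because a position missed at collection cannot be restored from any record the protocol describes.

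**What to change.** - **Label and data record (sections 5.1 B and 6.2 A):** add trap number and position (indoor/outdoor) to each bag, and carry both into the database before addresses are erased.
- **Layout (section 5.1 B):** where feasible, use the same number of traps and the same indoor/outdoor split of sheltered positions at every school, and one position type at all homes. Recording alone is the weaker remedy: if position is uniform within each school, 2-3 schools per type leave little to separate it from site.
- **Analysis (section 9 or the analysis plan):** compare catch per trap-week by typology within position, or adjusted for it, and build the school-density covariate in the same way.

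The cost is a wording change and two more label fields. Schools with no sheltered outdoor spot contribute indoor data only and so enter only the indoor comparison.

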#### **C. Questionnaire**

A questionnaire about knowledge, attitude and practice about dengue infection, chikungunya infection, prevention, and control measure will be administered to the parents/care givers of the participating children (1000).

### **5.2. Compensation**

Parents will receive 500 Baht for answering the KAP survey.

Children (100) participating in the mosquito collections at their homes will receive 1000 Baht per month for a maximum of 4 months.

### **5.3. Benefits to the individual and the community.**

The major benefit of the study is to generate first insight into the relationship between place of school and residence (defined by centrality and environmental typology) and risk of exposure to DENV and CHIKV. The study will also generate sero-prevalence data, which can then guide the local public health authorities for any potential implementation of the Takeda QDENGAR® (Dengue Tetravalent Vaccine [Live, Attenuated]) under evaluation for authorisation in Thailand. Knowledge of sero-positivity to the dengue virus will also be of direct benefit to the individual, especially with regard to the above-mentioned vaccine. Moreover, data from KAP about mosquito-borne diseases, control measures, and vaccine acceptance can contribute to the public health prevention campaigns concerning mosquito-borne diseases.

## **6. BIOLOGICAL SAMPLE COLLECTION**

### **6.1. Samples description**

#### **A. biological samples of human**

Finger-prick blood samples for use on a Rapid diagnostic lateral flow test (RDT) from 1000 children. No samples will be kept.

#### **B. biological samples of mosquitoes**

Mosquitoes caught on the sticky traps in the schools and homes will be identified to gender and species. There is no use of insecticides in these traps, just glue on paper.

### **6.2. Sample flow**

#### **A. Labelling**

The mosquito sticky paper catches will be changed weekly and placed into a ziplock bag with the date and address written in indelible ink on the outside of the bag and collected as soon as possible (days) by the entomological team.

#### **B. Shipment**

The mosquito sticky catches will be transferred to the entomology laboratory at Chulalongkorn University and identified to species and gender. Once identified and entered into the computer the samples will be disposed of. Once the mosquito sampling is complete, as above, the school/house address will be transformed into one of the four environmental categories. The address will then be erased.

#### **C. Storage**

There will be no storage of samples.

### **6.3. Biological analyses**

All RDT analyses will be performed on site in the schools. Mosquitoes will be identified by the entomologists of Chulalongkorn University. The RDTs and the mosquito samples will be disposed of once the results are known.

### **6.4. Human genetic analyses (if applicable)**

None

### **6.5. Secondary use of samples**

None

## **7. DATA COLLECTION AND DATA MANAGEMENT**

### **7.1. Data collection**

#### ***For connectivity and environmental typology of the area within which the individual goes to school and lives***

As shown above (Figs 1 & 2), Bangkok has previously been mapped using Twitter, Google POI, Facebook and transport information to define the centrality level of each sub-area and satellite images and built-up databases for its environmental typology.

#### ***For sero-conversion study (specific data collection):***

For each participating child, the age, gender, history of infection/ dengue vaccination, school name and address, house address and RDT test results for both dengue and Chikungunya will be written on the Case Report Form (CRF) immediately following the test. Information on age, sex and history of infection/ dengue vaccination will be obtained. We will also collect the school and place of residence coordinates (longitude & latitude), which will be subsequently classified in one of the four typologies Central+/Environmental+, Central+/Environmental-, Central-/Environment+, Central-/Environment aggregated to the scale of the grids as shown in Figures 1 & 2 and the coordinates information then erased.

#### ***For mosquito data***

BioGents Gravid Aedes Traps will be implemented in all participating schools for a period of one year and monitored weekly. These traps use sticky paper (glue) to capture flying adult mosquitoes. There is no use of insecticides. From May to September children in these schools will also be invited to take a trap home and collect mosquitoes in / around their homes.

#### ***For weather data***

We will use i-Buttons affixed to the GAT traps to measure temperature and relative humidity.

#### ***For questionnaire data***

Answers about KAP about mosquito-borne disease as Yes/No or composited score which will be standardized to a scale of 0-100%; 80-100% is considered a high score, 50-80% a moderate score and 50% or below a low score.

### **7.2. Data management**

The data will be input twice into two separate Xcel files and cross-checked. The address will be geolocated and then transformed to one of the four environmental categories before being erased.

For all types of data (sero-prevalence, mosquito and KAP), once the data has been entered (double entry and cross-check), all paper forms will be destroyed.

The sero-prevalence data will be maintained and analysed in the Pediatric department, Chulalongkorn University. The list of school and home addresses (coordinates) will be transformed into environmental typology by the IRASEC team present in Bangkok and this typological information sent back to the Pediatric department and linked to their sero-prevalence database. Once this link has been made and double checked, the coordinates information will be erased. The Institut Pasteur team will perform the statistical analysis with the Pediatric team in Chulalongkorn as described below.

The mosquito data will remain in the entomology department, Chulalongkorn University, and as above the coordinates linked to the environmental typology and subsequently analysed as described below.

The KAP data will be maintained and analysed in the Pediatric department, Chulalongkorn University. Once entered into the computer the address will be erased and the analysis performed as described below.

Only aggregated (analysed) data will be transferred to France for publication writing.

| Limited data from the professionals in charge of the clinical investigation and its organization           |                                                                                                                                                                                                |
|------------------------------------------------------------------------------------------------------------|------------------------------------------------------------------------------------------------------------------------------------------------------------------------------------------------|
| Data                                                                                                       | Justification                                                                                                                                                                                  |
| Personal data: last name, first name, e-mail, telephone number, postal address, guardian/trusted person... | Contacting participants to set up appointments, returning overall and/or individual results, maintaining communication with participants during the research, exercising participants' rights. |

| Data available to investigators and scientists for research                                                                                |                                                                                                                       |
|--------------------------------------------------------------------------------------------------------------------------------------------|-----------------------------------------------------------------------------------------------------------------------|
| Data                                                                                                                                       | Justification                                                                                                         |
| Identification data : participant code                                                                                              | Linking a participant's data set and samples                                                                          |
| Demographic data : age, gender, level of instruction,                                                                               | Describe the study population                                                                                         |
| Medical data : history of dengue and chikungunya infection, dengue vaccination and RDT test results for both dengue and chikungunya | Describe the general clinical pattern of the subjects studied for sero-conversion study.                              |
| Localisation : school name and address, home address, environmental typology                                                        | Connectivity and environmental typology of the area within which the individual goes to school and lives              |
| Assessment on dengue and chikungunya among parents                                                                                  | Describe the knowledge, attitude, and practice about mosquito-borne disease, control measures, and vaccine acceptance |

